
#### Data monitoring

This intervention is considered to be of the low-risk nature. Based upon the Research Ethics Office at St. Michael’s Hospital (Toronto, ON) guidelines, because of this low-risk nature of the intervention, a Data Monitoring Committee (DMC) was not required.

#### Potential study harms

Evidence suggests that serious adverse events (SAEs) are not anticipated in this specific trial design. However, there is the chance that minor SAEs may occur. Minor SAEs include, but are not limited to, parent’s concern regarding confidentiality, parents questioning the reasoning behind their child’s recruitment for the study (i.e., Child is at risk for obesity), and any conflict that may arise in the group facilitation sessions. These potential minor SAEs will be reported to the Research Ethics Office at St. Michael’s Hospital.

#### Trial auditing

To review trial conduct, the PARENT Trial project management team meets on a biweekly basis where status updates are shared, and decisions are finalized around plans for the study. In addition, the PARENT Trial project coordinator meets with the TARGetKids! Operations Team on a weekly basis to share updates around the PARENT trial, discuss strategies and issues in relation to the cohort, innovate (with the other programmers, developers, coordinators, and clinical research specialists in attendance), and resolve any runway issues pertaining to the project database and/or data collection.

### Statistical analysis of clinical data

Appropriate descriptive statistics for baseline characteristics (frequencies and proportions for discrete variables; means and standard deviations for symmetric variables; and medians and inter-quartile ranges for skewed data) will be used to compare groups. The principle of intention-to-treat will be applied to the analysis of outcomes. Outcome variables will be compared between arms using ANCOVA with the corresponding baseline measure as the covariate. For the primary outcome, the following additional covariates will be included: age and each of the risk indicators—(i) birth weight greater than 3500 g, (ii) weight gain in the first year of life, (iii) maternal or paternal obesity, (iv) smoking during pregnancy, and (v) mean family income less than $80,000. Mean differences and corresponding confidence intervals will be calculated. A two-sided level of 0.05 will be applied for the primary outcome. To determine if the treatment effect on the primary outcome depends on baseline BMI, the interaction term between the treatment group and baseline BMI will be added to the covariate model. If this term is significant at the 0.1 level, then sub-groups determined by baseline BMI will be examined.

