### Clinical outcome variables

The primary outcome measure will be the difference in age- and sex-standardized BMI *z*-score at 12 months post-randomization in the intervention and control groups. zBMI will also be measured at 6 months post-randomization. BMI is the key obesity-related outcome used in prevention and treatment trials in obesity and is the Canadian standard for growth monitoring, using the World Health Organization Growth Chart [19, 20]. Secondary outcomes will include physical activity, screen time, sleep duration, eating behaviors, family psychosocial health, cardiometabolic risk (blood pressure, waist circumference, non-HDL, HDL, triglycerides, total cholesterol, glucose, insulin), and mental health outcomes in the children. Sociodemographic measures will be collected via a questionnaire. We will examine healthcare utilization outcomes for children and their mothers through secondary data in partnership with The Institute of Clinical Evaluative Sciences (https://www.ices.on.ca/). For a more detailed overview of all measures, please see Table 1.

**Table 1 Tab1:** Outcome measures for the PARENT trial

Primary outcome		
Outcome		Outcome measure
Age- and sex-standardized BMI (6- and 12-month follow-up)		zBMI [32]
Secondary outcomes		
Child outcomes		Outcome measure
Child anthropometry and adiposity (baseline and 6- and 12-month follow-up)	Height Weight Head circumference Arm circumference Waist circumference	Measurement of child height (or length for children under 2) and weight is performed using standardized anthropometric protocols [33–35]. The WHO Growth Standards will be used to transform BMI to age- and sex-standardized *z*-scores [36]
Child cardiometabolic risk (baseline and 6- and 12-month follow-up)	Systolic and diastolic blood pressure	National High Blood Pressure Education Program (NHBPEP) [37]
	Non-fasting blood samples (only baseline and 12-month follow-up)	A trained health professional experienced with pediatric blood collection will collect 9–12 ml of blood. Topical anesthetic cream (e.g., EMLA or Ametop) will be offered to minimize discomfort from venipuncture. The blood samples include complete blood count, alkaline phosphatase, glucose, insulin, triglycerides, HDL, LDL, total cholesterol, non-HDL, ferritin, 25-OH vitamin D, CRP, and ALT [37]

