The coaching visits will be approximately 30–40 min long and delivered by a public health nurse. The coaching visits will integrate health messages and parenting skills addressed in other intervention components and encourage families to incorporate healthy nutrition and health behaviors individualized for their unique home and family environments through effective parenting practices learned in the program. The public health nurse will also link participants to local community resources where appropriate to support individual child and parental health and mental health identified during the coaching visits; referral will be facilitated by tools such as the Toronto Early Childhood and Family Resource System [23]. Finally, the coaching visits will be used to discuss participant progress, set and monitor personalized goals, and answer any questions. The criteria for a participant to discontinue the intervention are completed through participant request. The outcome data to be collected for participants who discontinue from intervention protocols is the same outcome data as those who attend the intervention parenting sessions (regardless of the degree of participation).

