### Sample size

The sample size calculation is based on an ANCOVA for the primary outcome zBMI at 12 months, using the baseline zBMI as a covariate. The total sample size of 108 (54 per arm) is based on the following criteria: a two-sided, level 0.05 test of the null hypothesis of no difference; power of 0.80; smallest clinically important difference is 0.5 zBMI units at 12 months; between-subject standard deviation is 1 unit; and within-subject correlation is 0.638, derived from TARGetKids! dataset of subjects meeting criteria (*n* > 700). Lost-to-follow-up is estimated at 10% [26, 27]. Obesity intervention trials in young children with 15–50 children per group have demonstrated significant treatment effect sizes of 0.3–0.5 units of zBMI [10].

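### The primary ANCOVA of 12-month zBMI leaves out the 6-month zBMI the trial already collects; a repeated-measures model would be a cheap, modest improvement

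*Protocol article*

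**What the plan says.** Clinical outcome variables fixes the primary endpoint as the between-arm difference in zBMI 12 months after randomization. The next sentence adds that "zBMI will also be measured at 6 months post-randomization", and the primary-outcome row of Table 1 lists both visits.

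Statistical analysis of clinical data gives the principle ("The principle of intention-to-treat will be applied to the analysis of outcomes") and the model ("Outcome variables will be compared between arms using ANCOVA with the corresponding baseline measure as the covariate"). For the primary outcome it adds age and five risk indicators. It names no 6-month term and no repeated-measures model.

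The Sample size section is also built on an ANCOVA of 12-month zBMI with baseline zBMI as covariate. It states the expected loss ("Lost-to-follow-up is estimated at 10", in percent).

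For families who stop the intervention, the Intervention section says that what is collected "is the same outcome data as those who attend the intervention parenting sessions (regardless of the degree of participation").

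**The concern.** An ANCOVA at one time point has no row for a child without the 12-month value. If 10% are lost, that is 0.10 × 108 = 10.8, or about 11 of the randomized children. Some of them will have a 6-month zBMI, which is a later and probably closer predictor of the missing value than baseline. The named model cannot use it.

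Continued follow-up after stopping the intervention deals with non-adherence, not with children who are lost. Parents know their allocation, and only the intervention arm carries eight 2-hour sessions plus coaching visits, so loss could differ by arm. Whether it will is unknown. If loss in one arm follows how the child is doing at 6 months, the children left at 12 months are no longer comparable given baseline alone, and the estimated effect shifts. A model that conditions on the 6-month value as well needs a weaker assumption about loss.

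**Working it through.** **Inputs from the article.** Two-sided level 0.05, power 0.80, difference 0.5 zBMI, SD 1, baseline to 12-month correlation 0.638, 108 children (54 per arm), loss 10%.

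**Inputs assumed (not in the article).** Correlation 0.70-0.80 between 0 and 6 months and 0.75-0.85 between 6 and 12 months; log-odds of loss rising by 0.5-1.5 per zBMI unit at 6 months; every lost child has a 6-month value, unless stated otherwise.

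**1. The plan's own figure, and power.** The ANCOVA residual variance is 1 − 0.638² = 0.593. The normal formula gives n = 2 × (1.960 + 0.842)² × 0.593 / 0.5² = 37.2, so 38 per arm (39 by the t distribution). Dividing by 0.9 gives 43-44 per arm, or 86-88 in total. The stated 108 is not reproduced and is larger than these inputs need. That is a separate matter, but it settles the power question. With 54 × 0.9 = 48.6 children per arm at 12 months, SE = √(2 × 0.593 / 48.6) = 0.156 and power is about 0.89. Dropping the lost children leaves power above 0.80.

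**2. Bias of ANCOVA on children with a 12-month value.** Simulation with 1,000,000 children per arm per scenario, true effect −0.5, 10% loss in each arm. Negative bias exaggerates the benefit.

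| Loss related to 6-month zBMI | ANCOVA without imputation | Using the 6-month value |
|---|---|---|
| Alike in both arms | about 0 | about 0 |
| Intervention arm only, slope 0.5 | −0.012 to −0.020 | about 0 |
| Intervention arm only, slope 1.0 | −0.022 to −0.038 | about 0 |
| Intervention arm only, slope 1.5 | −0.030 to −0.051 | about 0 |

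The one-arm range is thus about 0.01-0.05 zBMI. Relative to the target this is 0.012/0.5 = 2% to 0.051/0.5 = 10%. Relative to the standard error it is 0.012/0.156 = 0.08 to 0.051/0.156 = 0.33.

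**3. Other loss patterns**, slope 1, with 6-12-month correlations of 0.70-0.85:
- Random loss, or loss depending on baseline zBMI: about 0.
- One-arm dependence with unequal loss (5% against 15%): −0.036 to −0.047, brought to about 0 by the 6-month value.
- Opposite slopes in the two arms: −0.048 to −0.066, also brought to about 0.
- Loss in one arm depending on the unseen 12-month value: −0.053 to −0.057, still −0.025 to −0.046 with the 6-month value.

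**4. Precision.** Let r be the 6-to-12-month correlation given baseline, r = (b − 0.638a) / √[(1 − a²)(1 − 0.638²)], where a and b are the 0-6 and 6-12-month correlations. Over the assumed grid r runs from 0.52 (a = 0.80, b = 0.75) to 0.74 (a = 0.80, b = 0.85). With loss L and a fraction q of the lost children having a 6-month value, the variance falls by r² × [1 − (1 − L)/(1 − L + qL)]. For L = 0.10:
- r = 0.52, q = 0.5: 0.27 × (1 − 0.90/0.95) = 1.4%.
- r = 0.735, q = 1: 0.54 × 0.10 = 5.4%.

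The gain is therefore about 1-5% in variance.

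**The case against.** A reader might infer that the plan contradicts itself: it claims intention-to-treat but analyses completers only. The text does not support that. Nowhere does the article restrict the analysis to completers or exclude children without a 12-month value, and ANCOVA can be combined with imputation. An article commonly leaves missing-data handling to the full protocol or SAP, and neither is shown. Collecting outcomes whatever the degree of participation also supports the principle.

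Three further points carry weight:
- Table 1 lists zBMI at both visits, so the 6-month value may be compared in an ANCOVA of its own. It is still absent from the 12-month model.
- Baseline-adjusted ANCOVA at the endpoint is a standard choice and matches the sample-size method. Bias needs loss related to outcome that differs by arm, and parents are not told that zBMI is the primary outcome, which makes such loss less likely.
- One might fear large listwise losses from missing risk indicators. The article gives no missingness rates, and the indicators closely follow the eligibility risk factors, so no figure can be put on this.

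These points remove the charge of contradiction and keep the size small. They do not touch the remaining point: the named model leaves out a closely related measurement of the same outcome that the trial will hold.

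**Conclusion.** The point holds as a cheap improvement, not as an error or a contradiction. The stated primary model is a single-time-point ANCOVA without the 6-month zBMI; if run without imputation, about 11 of 108 children add nothing to it. Power is not at risk. The possible bias is about 0.01-0.05 zBMI at 10% loss if loss follows 6-month zBMI in one arm only, somewhat more if slopes are opposite in the two arms, and about zero if loss works alike in both. These sizes rest on the assumed correlations and loss slopes, and their removal rests on lost children having a 6-month value. The precision gain is about 1-5% in variance. The benefit is real but modest, and worth taking because it costs almost nothing.

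**What to change.** Make the primary analysis a likelihood-based repeated-measures model (a constrained longitudinal model or MMRM) with zBMI at baseline, 6 and 12 months, arm-by-visit terms, the planned covariates and an unstructured covariance. Keep the 12-month arm contrast as the primary comparison, so the endpoint does not change, and keep the planned ANCOVA as a sensitivity analysis. If the full protocol or SAP already does this, one sentence in the Statistical analysis section settles it.

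The cost is wording and a slightly more complex model; no new data and no change to the sample size are needed. The model does not fully protect against loss that depends on the unseen 12-month value, and it recovers little for children lost before 6 months.

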#### Inclusion criteria

Young children (18–48 months) identified as being at increased risk for childhood obesity will be eligible and invited to participate. The following risk factors, identified in the literature, will be used: a birth weight greater than 3500 g [14], weight gain in the first year of life (crossing of at least one percentile line of weight-for-length or zBMI percentile) [15], maternal or paternal overweight and obesity (BMI ≥ 25) [16], gestational smoking [17], and a low median household self-reported income [18]. Availability of at least one parent (caregiver) to participate in the study will be required.

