	Diet intake, physical activity, sedentary behavior, and sleep duration	The NHQ is an age-specific TARGetKids! instrument based on the Canadian Community Health Survey and Canadian Health Measures Survey. Domains include outdoor free play [38]; sedentary behaviors, child daily screen time [39], and sleep quality and duration; and sociodemographic factors (parent self-reported income, maternal education, ethnicity, immigration status, and marital status). Parental health, mental health, exposures during pregnancy (e.g., nutrition, medication, and vitamin use), and family medical history
	Dietary intake	NutriSTEP® questionnaire for toddlers (18–35 months) and preschoolers (3–5 years) [40]. The NutriSTEP® is a parent-administered, validated 17-item nutrition screening tool that has been developed to assess nutritional risk and includes topics of dietary intake (including fruit and vegetable intake, fast food intake), physical activity and screen time, physical growth and development/weight concerns, and factors affecting food intake (food security, psychosocial feeding environment) validated to identify children with nutritional risk in multicultural Canadian children [40]
	Direct physical activity levels (only baseline and 12-month follow-up)	The Actical accelerometer device worn for 24 h on three consecutive days will provide direct measures of physical activity [41–43]
Child Mental Health and Development (baseline and 6- and 12-month follow-up)	Mental health	The Strengths and Difficulties Questionnaire (SDQ) consists of 25 items subdivided into four difficulties scales, emotional symptoms, conduct problems, inattention-hyperactivity, and peer problems, and a separate fifth strength scale, prosocial behavior [44]. The SDQ Total Difficulties Score (TDS) can be calculated as the sum of the scores for the emotional symptoms, conduct problems, hyperactivity in attention, and peer problem subscales (range 0–40). Scores from the SDQ have been found to be highly correlated with the Child Behavior Checklist which correlates with mental health disorders in adolescence and adulthood [45]. There are two SDQ versions, one for children ages 2–4 and one for children ages 4–17

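### Age is a covariate only for zBMI, which is already age- and sex-standardized; age-dependent child secondary outcomes are adjusted for baseline alone, at a modest cost in precision

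*Protocol article*

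**What the plan says.** In the Protocol article, Statistical analysis of clinical data, two adjacent sentences fix the covariates. The general rule is: "Outcome variables will be compared between arms using ANCOVA with the corresponding baseline measure as the covariate". The exception follows: "For the primary outcome, the following additional covariates will be included: age and each of the risk indicators". Five risk indicators are then listed. Sex is listed for no outcome.

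The outcomes are described under Clinical outcome variables and in Table 1:

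- BMI: "The WHO Growth Standards will be used to transform BMI to age- and sex-standardized" z-scores. No other measure is stated to be standardized in this way.
- Secondary outcomes: "Secondary outcomes will include physical activity, screen time, sleep duration, eating behaviors, family psychosocial health, cardiometabolic risk (blood pressure, waist circumference", followed by lipids, glucose, insulin and mental health.
- Blood pressure: the measure column gives only "National High Blood Pressure Education Program (NHBPEP" with its abbreviation closed. It does not say whether values are analysed in mmHg or standardized.
- Activity, screen time and sleep: "The NHQ is an age-specific TARGetKids! instrument"; no standardized score is described.

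Inclusion criteria: "Young children (18–48 months) identified as being at increased risk for childhood obesity will be eligible". Randomization and blinding stratifies by practice site only, so nothing in the design balances age or sex.

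**The concern.** Age is given to the outcome that needs it least and withheld from those that may need it more. Over an entry range of 30 months, waist circumference, blood pressure, activity and sleep can be expected to vary with age. Whatever part of that variation the baseline value does not carry stays in the residual and widens the intervals.

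For some questionnaires the baseline value cannot carry all of it, because Table 1 changes the instrument with age. The dietary screen has a toddler version (18–35 months) and a preschool version (3–5 years). The mental health questionnaire has versions for ages 2–4 and 4–17. A baseline and a 12-month score may therefore come from different versions, depending on age at entry.

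At stake is the precision of the secondary estimates in a trial of 54 children per arm. The validity of the comparisons and the primary analysis are not at stake.

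**Working it through.** **Stated figure.** The article gives no precision or power figure for any secondary outcome, so there is none to reproduce. Its sample size is for zBMI and is used here only as a source of inputs.

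**Inputs from Sample size.** 108 children (54 per arm); 10% loss, so 108 × 0.90 ≈ 97 completers; correlation of baseline with 12-month zBMI 0.638. No correlation is given for any secondary outcome, and no correlation with age for any outcome.

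**Assumptions.** Age correlates equally (r_age) with the baseline and 12-month values, and linearly. ρ is the baseline to 12-month correlation of the outcome.

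**Gain from adding age to a baseline-adjusted ANCOVA.**

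partial r = r_age(1 − ρ) / √[(1 − ρ²)(1 − r_age²)]; SE ratio = √(1 − partial r²)

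Example, ρ = 0.638 and r_age = 0.5: partial r = 0.5 × 0.362 / √(0.593 × 0.75) = 0.181 / 0.667 = 0.271. Its square is 0.074, so the SE ratio is √0.926 = 0.962, a reduction of 3.8%.

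Reduction in SE, before the cost of the extra covariate:

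| ρ | r_age 0.1 | 0.2 | 0.3 | 0.5 | 0.6 |
|---|---|---|---|---|---|
| 0.3 | 0.3% | 1.1% | 2.7% | 9.4% | – |
| 0.5 | 0.2% | 0.7% | 1.7% | 5.7% | 9.9% |
| 0.638 | 0.1% | 0.5% | 1.1% | 3.8% | 6.4% |
| 0.8 | 0.1% | 0.2% | 0.6% | 1.9% | 3.2% |

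The formula gives 16.5% for the empty cell. I leave it out because 0.6² = 0.36 exceeds 0.3: baseline and follow-up would then correlate negatively among children of the same age, which is not plausible.

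At ρ = 0.638, a comparison with 80% power would move to 80.1% (r_age 0.1), 80.9% (0.3), 82.9% (0.5) or 84.9% (0.6).

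**Cost.** Baseline-only ANCOVA leaves 97 − 3 = 94 residual degrees of freedom. The SE penalty is roughly √(94/93) = 1.005 for one covariate, √(94/92) = 1.011 for two and √(94/91) = 1.016 for three. With age and sex at ρ = 0.638, and sex carrying no information, the net SE is 1.0% higher at r_age 0.1, 0.6% higher at 0.2, unchanged at 0.3, 2.7% lower at 0.5 and 5.4% lower at 0.6.

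**Chance imbalance.** If entry age is uniform over 18–48 months (assumed), its SD is 30/√12 = 8.66 months. The SE of the difference between arms is 8.66 × √(2/54) = 1.67 months, and 1.96 × 1.67 = 3.3 months. The article does not allow this to be turned into a shift in any outcome.

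**Questionnaire versions.** Adding 12 months to entry age gives, for the dietary screen: entry at 18–23 months, toddler version both times; 24–35 months, toddler then preschool; 36–48 months, preschool both times. For the mental health questionnaire, children under 24 months fall below the youngest listed version at baseline, and those entering at 36–48 months have reached the version boundary by follow-up.

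**The case against.** A reader might infer that secondary outcomes are compared raw. They are not: each is adjusted for its own baseline, and a child's baseline waist or blood pressure already reflects much of that child's age and sex. This stands, and it is why the gains above are small when tracking is good.

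A reader might also infer that the estimates are biased, or that a chance age difference invalidates them. Randomization rules out the first, and the confidence interval already allows for the second.

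Nor is it established that BMI alone is standardized. It is the only measure stated to be. For blood pressure the scale is open, the activity and sleep questionnaire is called age-specific, and the developmental screen uses age-specific milestones. These features do not show that scores are standardized, but they rule out a flat claim that none are.

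The strongest objection is that covariates for secondary outcomes belong in an analysis plan or in the full protocol, which the article says is available on request. That would settle the matter if the article were silent. It is not silent: it gives a covariate rule for all outcomes and confines age to one of them. An unseen document may still add terms, which limits the weight of the point.

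Finally, adding covariates leaves the estimate in its original units. It does not answer the complaint that a centimetre or a mmHg means different things at different ages; only a standardized scale would.

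**Conclusion.** The point holds as a minor matter of efficiency. The stated rule adjusts for age where the outcome is already standardized for it, and omits age and sex for child measures that are not stated to be.

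The expected gain is about 0–6% in standard error at a baseline correlation near 0.64. It is 9–10% only where tracking is poorer (0.3–0.5) and age dependence strong (0.5–0.6), and the article shows neither for any outcome. Where age dependence is weak, two extra covariates can cost up to about 1%. These figures rest on assumed age correlations, on a correlation borrowed from zBMI, and on age being equally related to both measurements. Where the questionnaire version changes between visits that last assumption is doubtful, and the gain could differ from the table. The primary outcome, its model and the sample size are untouched.

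**What to change.** In Statistical analysis of clinical data, add a sentence prespecifying age at baseline and sex as further covariates in the ANCOVA of each child secondary outcome that is not already age- and sex-standardized. For blood pressure, state the scale: either add height to those covariates, or analyse values standardized for age, sex and height. For questionnaires whose version changes with age, state how scores from different versions are handled; an age term absorbs a shift in level but not a change in the baseline slope.

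Age, sex and height are already collected. The cost is two degrees of freedom per model, or three for blood pressure with height. The change should be fixed before any unblinded analysis.

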#### Randomization and blinding

Individual children will be randomized based on a stratified randomization technique, ensuring equal recruitment of intervention and control participants for each practice site, executed via computer-generated random allocation sequence, in variable block sizes (i.e., 2, 4, 6). Contamination will be addressed by delivering the parenting group sessions after hours or online, and we will record all participants’ participation in other community-based services. To reduce the risk of bias, research assistants who will not be part of the delivery of the intervention will collect all outcome data, and data analysts will be blinded to group allocation. Parents cannot be blinded to the study allocation; however, they will be blinded that the primary outcome is zBMI.

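### Randomization is stratified by practice site but the ANCOVA models omit site; if site predicts outcome, the reported intervals are somewhat too wide and the test conservative

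*Protocol article*

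**What the plan says.** Under Randomization and blinding, the protocol article states: "Individual children will be randomized based on a stratified randomization technique, ensuring equal recruitment of intervention and control participants for each practice site". The sequence is computer-generated, with variable blocks of 2, 4 and 6. No other stratification factor is named.

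Under Statistical analysis of clinical data, the general model is: "Outcome variables will be compared between arms using ANCOVA with the corresponding baseline measure as the covariate". The model for zBMI at 12 months is then extended, in these words: "the following additional covariates will be included: age and each of the risk indicators". Five numbered indicators come after that: birth weight, first-year weight gain, parental obesity, smoking in pregnancy and family income. Practice site is in neither model, and no other section says that the analysis accounts for the stratification.

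The Sample size section rests on an ANCOVA with baseline zBMI as covariate, "a two-sided, level 0.05 test of the null hypothesis of no difference" and power 0.80. Its other inputs are a target effect ("smallest clinically important difference is 0.5 zBMI units at 12 months"), a spread ("between-subject standard deviation is 1 unit"), a correlation with baseline ("within-subject correlation is 0.638") and 10% loss to follow-up.

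**The concern.** Blocking within site balances the arms on site, so differences between sites largely drop out of the treatment contrast. A model without site leaves those differences in the residual variance. The standard error is then computed as if allocation had been unrestricted and comes out larger than the estimator's real variability.

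Site could plausibly matter here. The Discussion part of the Abstract describes socially, culturally and geographically diverse practices in three models of primary care. Eligibility and recruitment says that outcomes are collected by research staff embedded at each practice. Site may therefore carry differences in both population and measurement. The secondary outcomes lack even the indirect protection that the risk indicators give the primary model.

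At stake are the width of the reported intervals and a little power, in a trial of 108 children.

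**Working it through.** **The plan's own figure.** The article has no figure for a site effect. Its stated N was checked first.
- Residual SD under ANCOVA: √(1 − 0.638²) = 0.770.
- n per arm = 2 × (1.96 + 0.842)² × 0.770² / 0.5² = 37.2, so 38 (39 with the t distribution).
- Dividing by 0.9 for loss gives 43 (44) per arm, or 86 (88) in total.

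The stated 108 is not reproduced. It errs on the large side, is a separate matter and does not affect this point.

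**Planned precision.** After 10% loss, 54 × 0.9 = 48.6 children per arm remain. SE = 0.770 × √(2/48.6) = 0.1562. Power at 0.5 is Φ(0.5/0.1562 − 1.96) = 0.893.

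**Idealized effect of omitting site.** Let R be the site share of the residual variance (assumed; not in the article), with perfect balance within site and no cost in degrees of freedom.
- Actual type I error without site: 2[1 − Φ(1.96/√(1−R))].
- Power without site: Φ((0.5/0.1562 − 1.96)/√(1−R)).
- Power with site: Φ(0.5/(0.1562√(1−R)) − 1.96).

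| R | Type I error, no site | Power, no site | Power, with site |
|---|---|---|---|
| 0 | 0.050 | 0.893 | 0.893 |
| 0.05 | 0.044 | 0.899 | 0.907 |
| 0.10 | 0.039 | 0.905 | 0.921 |
| 0.15 | 0.034 | 0.911 | 0.935 |
| 0.20 | 0.028 | 0.917 | 0.947 |

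**Simulation.** This drops the perfect-balance assumption and counts the degrees of freedom. 98 completers were allocated in permuted blocks of 2, 4 and 6 within site, with outcome correlation 0.638 with baseline. ANCOVA on baseline was run with and without fixed site effects, with 4,000 runs under the null and 3,000 at a difference of 0.5. The number of sites is an assumption. Results for 8 sites (SE and type I error from the null runs):

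| Site share | Mean model SE, without / with | Type I error, without / with | Power, without / with |
|---|---|---|---|
| 0 | 0.156 / 0.156 | 0.049 / 0.050 | 0.872 / 0.868 |
| 0.05 | 0.155 / 0.153 | 0.048 / 0.051 | 0.899 / 0.899 |
| 0.10 | 0.155 / 0.148 | 0.036 / 0.046 | 0.904 / 0.920 |
| 0.20 | 0.154 / 0.140 | 0.034 / 0.046 | 0.915 / 0.944 |

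The Monte Carlo standard error of each entry is about √(0.05 × 0.95/4000) = 0.003 for type I error and √(0.9 × 0.1/3000) = 0.005 for power.

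At a 20% share the empirical SD of the estimate is 0.141 without site and 0.140 with it, so the estimate is almost equally accurate either way. What differs is the reported SE: 0.154 without site (0.154/0.141 = 1.09, about 9% too large) and 0.140 with site, which matches.

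**Other numbers of sites.** At a 20% share, type I error without site is 0.036 with 4 sites and 0.033 with 12, and the power gain is 2 to 3 points (0.914 to 0.936; 0.908 to 0.936). At a 10% share, type I error without site is 0.045 with 4 sites and 0.046 with 12, so the 0.036 at 8 sites is probably a little low by chance. With 12 sites and no site effect, fixed site terms cost about one point (0.896 to 0.886).

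**Limits of the simulation.** It omits age and the risk indicators, so the share must be read as what remains after all listed covariates. It also blocks the completers directly. Loss to follow-up would loosen the balance within site and so reduce the overstatement of the SE.

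**The case against.** The strongest reply is that the harm depends on a quantity the article does not give. What counts is the site share left after baseline zBMI, age and five risk indicators, including income. Much of any population difference between practices would act through these, and a persistent measurement difference would also show in the baseline value and be partly absorbed there. Measurements follow standardized protocols and are taken by trained network staff. A share below 5% is plausible, and there the simulation finds almost nothing. This stands, and it is why the range must start at zero.

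A second reply is that this is a condensed article and the handling of site may be set out in the full protocol or an analysis plan. That has some force for the secondary outcomes, which get one general sentence. It has little for the primary outcome, where the covariates are itemized down to an income cut-off and the stratification factor is not among them.

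A third reply is that site terms use degrees of freedom, and the number of sites is unknown. This is fair, and the fix must allow for it.

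A reader might also infer that the omission biases the treatment effect, invalidates the test or certainly wastes precision. The documents support none of these. Allocation is balanced within site, so the estimate stays unbiased. The error runs toward too few false positives. Any loss is conditional on site being prognostic, and it lies mainly in the reported SE and interval, not in the accuracy of the estimate.

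**Conclusion.** The point holds in a limited form. The stated models do not reflect the stated randomization. If site predicts the outcome after the listed covariates, the analysis is conservative: at 8 sites with 98 completers, the SE is about 9% too large and type I error is 0.034 at an assumed 20% share, with about 3 points of power lost. At a share of 5% or less the simulated effect is negligible, and with no site effect nothing is lost.

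Confidence is high for the omission and its direction and low for any particular size, because the site share and the number of sites are both assumed. Under the article's own inputs power is about 0.89 with 10% loss, against a planned 0.80, so the main conclusion is not put at risk. The change is worth making for consistency between design and analysis. The secondary outcomes were not simulated separately; the same mechanism applies, but its size for them is unknown.

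**What to change.** Add practice site to the ANCOVA for the primary and secondary outcomes and say that it is included because it is the stratification factor. Use a fixed effect if sites are few. If there are many small sites, use a random intercept, or state in advance a rule for pooling sites that recruit only a few children. Settle this before allocation is revealed to the analysts, so that the choice cannot look data-driven.

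The cost is one line in the model and, with fixed effects, one degree of freedom per additional site. If site has no effect, simulated power is 0.868 with site and 0.872 without at 8 sites, a difference within simulation error. The cost of about one point at 12 sites is the reason to keep the random intercept or pooling option open.
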